#### Baseline Assessment

The baseline data were collected from December 2019 to March 2020. During the baseline assessment, the mean ST, prevalence of excessive ST and its correlates, mean duration of physical activity, emotional problems, and sleep disturbances in both the intervention and control arms were measured.

To assess mean ST, physical activity, and prevalence of excessive ST, a pretested, validated, semistructured, bilingual (English and Hindi languages) digital screen exposure questionnaire (DSEQ) was used (Multimedia Appendix 7). The DSEQ was developed in 5 phases. In phase 1, a draft questionnaire was developed by reviewing the literature on existing tools (n=2) from 2009 to 2017. In phase 2, 9 experts assessed the draft Hindi and English questionnaires’ face and content validity. Face-to-face interviews with primary caregivers (n=30) were conducted in a tertiary care hospital for acculturation. In phase 3, a pilot study was conducted among randomly selected families to evaluate the feasibility of the DSEQ in field settings. During phase 4, test-retest reliability was assessed among 30 primary caregivers selected randomly in another urban cluster. In phase 5, the internal consistency of the DSEQ was checked by conducting a cross-sectional study among 400 randomly selected, primary caregivers in Chandigarh, North India. The DSEQ has good internal consistency (Cronbach α=0.73-0.82) and inter-rater agreement (kappa 0.75, 95% CI 0.72-0.78).

The DSEQ was used to collect information from the primary caregivers of the children on (1) sociodemographic profile including family type and socioeconomic status (BG Prasad classification, 2016) [42], (2) digital screen exposure and home media environment, (3) level of physical activity of the child, (4) child’s media-related behaviors, and (5) parental perceptions and literacy regarding digital screen exposure. We recorded the duration and content of media watched by the child on a typical day. The objective criterion to measure ST was the number of hours the child watched a specific TV program. Cinema and movies were excluded from the ST measurement to calculate the actual average of ST for a regular day. Besides, cinema and movies are not watched daily and might falsely increase ST.

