#### Implementing the Intervention

In this stage, the PLUMS intervention will be delivered over an 8-week period at the household level in the intervention arm, as already described (Supplementary Table 2 in Multimedia Appendix 5). The objectives of the intervention are to reduce the ST of children [18], enable the caregivers with positive parenting skills and ST literacy, and propose unplugged family time in the home environment.

Participants in the intervention arm will also be classified into 5 behavior stages of change as per the transtheoretical model [45]. In the control arm, routine home-based and facility-based health services will be continued by the local auxiliary nurse midwife under the public health system. Compliance of the intervention will be checked via a proforma from parents (Supplementary Table 3 in Multimedia Appendix 5) and via a journal, videos, or pictures maintained by families.

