#### Postintervention Assessment

In this stage, the same questionnaire for ST and its correlates as used in the baseline assessment will be administered to the intervention and control groups immediately and 6 months postintervention. Hence, primary and secondary outcome measures will be assessed at these 2 time points. In addition to the 2 months of active intervention, the researcher will maintain contact with the intervention arm group participants during the 6-month follow-up period. A passive intervention via information education material (text messages, telephone, emails, or mail) to parents will be given during the follow-up period.

This intervention study will take place over a period of 8 months. The baseline data collection will take place before the intervention (t_0_). The postintervention phase (t_1_) and follow-up assessment will be done at 6 months (t_2_), as shown in Supplementary Table 4 in Multimedia Appendix 5, as per the Standard Protocol Items: Recommendations for Interventional Trials (SPIRIT) [46].

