#### Outcomes

The primary outcome (caregiver-reported) measure will be the mean change in ST (in minutes) per day separately for weekdays and weekends. The secondary outcomes (caregiver-reported) will be the mean change in the duration of physical activity (in minutes), proportion of children with emotional behavior problems, and sleep disturbances. For emotional behavior and sleep disturbances, the change in scores as per the tools will be noted, as mentioned earlier.

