#### Data Management and Analysis

Quantitative data from the intervention study will be entered into Microsoft Excel and analyzed using SPSS for Macintosh, Version 25.0 (IBM Corp, Armonk, NY). ST on a weekday and weekend day will be calculated separately as per available literature [47]. So, the average ST (by viewing any type of media gadget) per day in a week will be calculated, and because there are 5 weekdays (Monday to Friday) and 2 weekend days (Saturday and Sunday) in a week, the weighted average ST per day in a week will be calculated as: Average ST per day (minutes) = [(Weekday ST in minutes x 5) + (Weekend ST in minutes x 2)]/7.

Continuous variables will be summarized as means with interquartile ranges and standard deviations. Correlations between a continuous variable and other variables will be estimated. Categorical variables will be summarized as proportions, and differences between groups will be tested using chi square tests. The data will be analyzed as per intention-to-treat analysis (for their initially assigned study arm) and per-protocol analysis. Relative risks and their effect sizes, together with the corresponding 95% CIs, will be estimated. The effectiveness of the intervention will be estimated by calculating the relative risk reduction (1-relative risk). A *P* value <.05 will be considered statistically significant for all analyses.

Information regarding PLUMS will be shared in the first communication and then reinforced every week for 8 weeks. So, participants who withdraw from the trial after the third week will be included in the analysis. Participants who withdraw any time before the third week will be excluded from the analysis.

Caregivers’ knowledge will be analyzed at the end of the intervention if no associations are observed. The proforma on behavior change will be completed at baseline (t_0_) and endline (t_1_) to determine the stage of change the families are at postintervention.

A feedback/compliance questionnaire (Supplementary Table 3 in Multimedia Appendix 5) will be given to the caregivers at each counseling session (weekly) to check their fidelity. The child's fidelity, including the level of engagement, will be checked with personalized journals comprising the activities they performed during the given intervention. The parents will be contacted via their preferred mode of communication weekly to keep them motivated and disseminate the next week's intervention module.

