### Strengths

The strengths of this study are that the participants represent Chandigarh's population; hence, the study results can be generalized. There are no published intervention studies from India in this age group and on ST [25]. This study will be the first study that provides a home-based intervention plan to families based upon commonly used theories (transtheoretical model of behavior change [33], social cognitive theory [54], and self-determination theory [25]). This intervention complies with the latest American Academy of Pediatrics guidelines (2016), while previous studies were based on older guidelines. Also, this intervention study focuses on enhancing parents’ literacy concerning ST and will eventually have a long-term effect.

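### The analysis of caregivers' knowledge, a stated target of the intervention, is made to depend on an undefined absence of associations elsewhere in the trial

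*Protocol article*

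**What the plan says.** The rule is a single sentence in Data Management and Analysis: "Caregivers’ knowledge will be analyzed at the end of the intervention if no associations are observed". No other section names an analysis of caregivers' knowledge.

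Four other places bear on it:

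- **Implementing the Intervention** includes among the objectives of the programme to "enable the caregivers with positive parenting skills and ST literacy".
- **Strengths** says that "this intervention study focuses on enhancing parents’ literacy concerning ST", and expects a long-term effect from this.
- **Baseline Assessment** gives, as the fifth area covered by the Digital Screen Exposure Questionnaire (DSEQ), "parental perceptions and literacy regarding digital screen exposure".
- **Postintervention Assessment** says that the baseline questionnaire for screen time and its correlates "will be administered to the intervention and control groups immediately and 6 months postintervention".

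Outcomes does not list knowledge. The primary outcome is "the mean change in ST (in minutes) per day separately for weekdays and weekends", and the secondary outcomes are "mean change in the duration of physical activity (in minutes), proportion of children with emotional behavior problems, and sleep disturbances".

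**The concern.** An analysis that is carried out because other analyses came out null is selective. A reader of the final report could not tell whether knowledge is shown because it was always of interest or because nothing else was found. Conversely, silence about knowledge after a positive result would say nothing about whether caregivers learned anything.

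The condition also runs against the logic of the programme. The caregiver module is meant to teach and motivate caregivers, who then model the behaviour and change the home media environment. Knowledge is an early step on that path. It is as informative after a positive screen-time result, when it helps to show how the effect arose, as after a null one, when it helps to show where the chain broke. The article plans it only for the second case.

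**Working it through.** The plan gives no figure on this point, so there is nothing to reproduce. The check is a comparison of sections.

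**1. Is knowledge a target of the intervention?** Yes. Implementing the Intervention names screen-time literacy as an objective ("enable the caregivers with positive parenting skills and ST literacy"), and Strengths repeats it ("this intervention study focuses on enhancing parents’ literacy concerning ST").

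**2. Is it a listed outcome?** No. Neither "the mean change in ST (in minutes) per day separately for weekdays and weekends" nor "mean change in the duration of physical activity (in minutes), proportion of children with emotional behavior problems, and sleep disturbances" includes it. The accurate description is a measured intervention target.

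**3. Would the data exist whatever the result?** Very probably. The DSEQ covers literacy, and the baseline questionnaire is repeated in both arms at both postintervention assessments without any condition. Feasibility therefore does not explain the rule. One step is inferred: the article does not say that knowledge in the conditional sentence means the DSEQ literacy section, though no other instrument described in the text covers it. The stage-of-change proforma in the same paragraph measures a different construct.

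**4. Can the trigger be applied reproducibly?** No. From Outcomes, Postintervention Assessment, and Data Management and Analysis, the word associations could refer to:

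- 3 screen-time measures (weekday, weekend, weighted daily average);
- 3 secondary domains (physical activity, emotional-behavioural problems, sleep);
- 2 postintervention time points;
- 2 analysis sets (intention-to-treat, per-protocol).

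That makes (3 + 3) × 2 × 2 = 24 comparisons, counting each secondary domain once. The article does not say which of them must be null, or whether one non-null result is enough to block the knowledge analysis. Two analysts with the same results could reach opposite decisions.

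**5. Is the timing coherent?** Not clearly. The sentence places the analysis at the end of the intervention. If the 6-month results count towards the trigger, its state cannot be known then.

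**6. Does the rule affect the primary test or the sample size?** No. It concerns only whether a non-primary measure is analysed.

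**7. What baseline is available for an adjusted analysis?** Baseline data were collected from December 2019 to March 2020, and the intervention started in November 2020 (Results). The interval is 8 months from March and 11 months from December. Results plans to re-measure only screen time and physical activity before delivery.

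**The case against.** The strongest defence is that this is a process analysis. The sentence stands next to the stage-of-change proforma and the fidelity checks, and looking at knowledge to explain a null result is a legitimate diagnostic step. That may well be the intention, but the article does not say so, and the diagnostic purpose does not require leaving knowledge out after a positive result.

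The text says if, not only if. General clauses in the same section, on correlations and on chi-square tests for categorical variables, could also cover literacy items. Both points are fair: it cannot be said that literacy would certainly go unreported in a positive trial, only that no analysis of it is named. A condition that restricts nothing would have no purpose, however, so the sentence needs correcting either way.

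An unseen analysis plan might handle this. The point concerns a rule that the article itself sets, not a detail it leaves out.

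Four stronger readings are tempting and are not supported:

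- **That an outcome of the trial is dropped when the trial succeeds.** Knowledge is not a listed outcome.
- **That knowledge becomes a substitute claim of success.** Study Objectives and Data Management and Analysis define effectiveness through screen time and relative risk reduction, and nothing lets a knowledge result take that place.
- **That the analysis would run in only 20% of trials if the assumed effect is real.** This is 1 − 0.80, one minus the planned power. It assumes that the undefined trigger is the primary test, and it does not measure harm.
- **That the rule inflates false positives because "value <.05 will be considered statistically significant for all analyses".** With independent tests, no true effects and one primary test as the trigger, the current rule gives 1 − 0.95² = 9.75% for at least one significant result. An unconditional comparison at two time points gives 1 − 0.95³ = 14.3%. By that measure the remedy does worse. The objection is to selection, not to the number of tests.

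**Conclusion.** The point holds in limited form. The article makes the analysis of a stated intervention target depend on an undefined absence of associations, so knowledge would be examined selectively after null findings and has no named analysis in a positive trial. The consequence is for reporting and for understanding the mechanism; the primary result, the sample size and the definition of effectiveness are untouched. No numerical size is claimed. The sentence should be corrected because it is a stated rule and is cheap to repair, but this is not a threat to the trial's main conclusion.

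Two assumptions remain: that knowledge means the DSEQ literacy section, and that the analysis intended is a comparison between arms. The article states neither. If a different analysis was meant, the sentence still has to say what it is and when it applies.

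**What to change.** Replace the conditional sentence with: Caregiver knowledge (DSEQ literacy section) will be compared between arms at t1 and t2, adjusted for its baseline value, in all randomised families with data and whatever the other results. This is an exploratory analysis of mechanism and cannot replace a null primary result.

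The cost is one sentence and one additional model, using data already planned for collection in both arms. It adds two exploratory comparisons, which is why the exploratory label and the final clause are needed.

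The literacy baseline dates from December 2019 to March 2020 unless literacy was re-measured together with screen time and physical activity before delivery. The article reports that delivery began in November 2020, so that opportunity may have passed. In that case the plan should state the date of the baseline used. An older value is still a pre-intervention covariate and would mainly cost precision.

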#### Ethics and Dissemination

Ethical approval was obtained from the institutes' ethics committee: Postgraduate Institute of Medical Education and Research, Chandigarh, India (INT/IEC/2019/000711, Dated 02/04/2019).

## Results

Enrollment of all participants (n=440) was completed during the baseline assessment. The intervention phase could not be started due to restrictions imposed under lockdown to contain the Covid-19 pandemic. Considering the Covid-19 pandemic and likely change in the ST and physical activity of the children, we will measure the ST and physical activity again before delivering the intervention. The intervention was started in November 2020. It will be implemented for 8 weeks. The endline assessment will be done immediately postintervention and after the 6 months of follow-up. The results will most likely be published by 2022.

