We used the 5 progressive physical activity levels among preschoolers given in the Preschool Physical Activity Questionnaire (PrePAQ) to assess physical activity. The PrePAQ categorizes activity into stationery (no action), sedentary (limb or trunk movement), slow-paced (moving easily or slowly), medium-paced (moving at a moderate pace), and fast-paced (quick pace or hard effort) [43].

The standard Preschool Child Behavior Check List was used to assess the child’s emotional and behavioral development. It has been validated in an Indian setting and has the right internal consistency (Cronbach α=0.95) [44]. It consists of 100 items with a 3-step response scale (0, 1, and 2). These items are scored as being absent (score, 0), occasionally present (score, 1), and very often present (score, 2).

The sleep disturbances scale for children was used to measure the child’s sleep patterns. It is a 26-item Likert-type scale that measures specific sleep disorders along with overall sleep disturbances in children. It has been validated and has an internal consistency of 0.71-0.79, test-retest reliability of 0.71, and diagnostic accuracy of 0.91 [40].

The lead author visited the homes of the study families and conducted face-to-face interviews during the baseline assessment.

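### As written, change in the behaviour and sleep scores runs from a pre-lockdown baseline 8-11 months before the intervention; ANCOVA at follow-up should replace the change score

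*Protocol article*

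**What the plan says.** The Baseline Assessment section dates the first measurement: "The baseline data were collected from December 2019 to March 2020". It covered all the outcome domains: besides screen time, "mean duration of physical activity, emotional problems, and sleep disturbances in both the intervention and control arms were measured". Screen time and physical activity come from one instrument, the digital screen exposure questionnaire. Behaviour comes from a separate 100-item checklist ("The standard Preschool Child Behavior Check List was used to assess the child’s emotional and behavioral development") and sleep from a separate 26-item scale.

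The Results section reports the delay: "The intervention phase could not be started due to restrictions imposed under lockdown to contain the Covid-19 pandemic". It expects screen time and physical activity to have shifted, and so "we will measure the ST and physical activity again before delivering the intervention". It then states: "The intervention was started in November 2020". The behaviour and sleep instruments are not named in that re-measurement.

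The Outcomes section nevertheless keeps change as the metric for these two domains: "For emotional behavior and sleep disturbances, the change in scores as per the tools will be noted". It also lists the proportions of children with emotional-behaviour problems and sleep disturbances. The Postintervention Assessment section puts t0 before the intervention in a study lasting 8 months, with assessments immediately after the 8-week programme and 6 months later.

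**The concern.** The plan accepts that lockdown made the first baseline out of date for screen time and physical activity. Its Introduction assumes that screen time may causally affect emotional behaviour and sleep as well as physical activity. On that premise, a shift in screen time large enough to need a new baseline would probably carry behaviour and sleep with it, yet only physical activity among the three is named for repetition.

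Two things are at stake. First, precision: the further a baseline lies from follow-up, the weaker its correlation with follow-up is likely to be, and a change score pays for that directly because it subtracts the whole baseline, noise included. Second, interpretation: in children aged 2-5, a within-arm change over 10 months or more mixes development and lockdown with anything the programme does. If the re-measurement serves as t0 for screen time and physical activity, the same label would then cover dates most of a year apart for different outcomes.

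**Working it through.** **Intervals.** The article states no interval, so there is no figure to reproduce. Inputs: baseline December 2019 to March 2020 (Baseline Assessment); start November 2020 and 8 weeks of delivery (Results); second endline 6 months after the first (Postintervention Assessment). Taking t1 as start plus 2 months (about January 2021) and t2 as t1 plus 6 months (about July 2021), calendar-month subtraction gives:

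| From the old baseline to | From March 2020 | From December 2019 |
|---|---|---|
| Start, November 2020 | 8 months | 11 months |
| t1, about January 2021 | 10 months | 13 months |
| t2, about July 2021 | 16 months | 19 months |

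Counted to the day, the gap to the start could be anything from about 7.1 months (31 March to 1 November 2020) to 12.0 months (1 December 2019 to 30 November 2020). A measurement just before delivery would instead lie about 2 months before t1 and 8 months before t2, which matches the stated study length.

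**Precision.** Let r be the baseline-to-follow-up correlation, with equal variances at both times, and express variances in units of the follow-up SD². Then:

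- follow-up score alone: 1
- change score: 2(1 − r)
- ANCOVA: 1 − r²
- ANCOVA relative to change score: (1 − r²) / [2(1 − r)] = (1 + r)/2, so the CI width ratio is √[(1 + r)/2]

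The documents give no r, so a range is shown:

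| r (assumed) | Change score | ANCOVA | CI width ratio, ANCOVA to change | CI narrower by |
|---|---|---|---|---|
| 0.6 | 0.80 | 0.64 | √0.80 = 0.894 | 11% |
| 0.5 | 1.00 | 0.75 | √0.75 = 0.866 | 13% |
| 0.4 | 1.20 | 0.84 | √0.70 = 0.837 | 16% |
| 0.3 | 1.40 | 0.91 | √0.65 = 0.806 | 19% |

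The change score's variance passes 1 when r falls below 0.5. From there, subtracting the baseline is worse than ignoring it. The ANCOVA variance stays below 1 throughout.

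**What a weaker correlation would itself cost.** If ageing of the baseline lowered r from 0.6 to 0.5, the change-score CI would widen by √(1.0/0.8) − 1 = 12% and the ANCOVA CI by √(0.75/0.64) − 1 = 8%. If r fell from 0.6 to 0.3, the figures would be √(1.4/0.8) − 1 = 32% and √(0.91/0.64) − 1 = 19%. ANCOVA therefore limits the damage as well as being the more precise method at each r.

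**The case against.** Four points on the other side have force.

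- **The word only is an inference.** The Results section lists what will be repeated and does not expressly exclude the other scales. The assessment schedule is in a supplementary table that is not shown. A reader might conclude that the scales were certainly not repeated, but the text does not go that far. It does name two domains, justify the repetition by reference to those two, and describe no other second measurement.
- **The between-arm comparison is not biased by this.** A reader might infer that lockdown and ageing contaminate the estimated effect on behaviour and sleep. They do not do so through the age of the baseline, which is the same for both randomised arms. Study Objectives defines effectiveness against the control group, and Data Management and Analysis plans comparisons by assigned arm. No within-arm efficacy claim is planned, nor any analysis relating change in screen time to change in sleep or behaviour, so it would also go too far to say that the plan tests that link on mismatched intervals.
- **Change scores are not the only metric.** The proportions with behaviour problems and sleep disturbances can be compared at follow-up without any baseline.
- **The size is assumed.** No correlation is given, the outcomes are secondary, and the sample size rests on screen time alone, so no stated power figure is affected.

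It could also be said that the choice between change score and ANCOVA belongs in an analysis plan. That would hold had the article been silent, but its Outcomes section names change in scores. All four points limit the consequence. None supplies a newer baseline for the two scores or makes the change score the better use of the old one.

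**Conclusion.** The point holds as one about precision and clarity for two secondary outcomes. On the text as it stands, the only documented baseline for the behaviour and sleep scores precedes the intervention by 8-11 months, t1 by about 10-13 months and t2 by about 16-19 months. Pre-lockdown is the safe description; pre-pandemic would claim more than a window running into March 2020 supports.

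Over assumed correlations of 0.6 to 0.3, with equal variances, the change score gives up 11% to 19% in CI width compared with ANCOVA on the same data, and is worse than the unadjusted follow-up score once the correlation is below 0.5. How far the correlation has actually fallen cannot be known from the documents. The recommendation does not depend on it: at every value in the range ANCOVA is the more precise, and its advantage is largest where the baseline is least informative.

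**What to change.** In Outcomes and in Data Management and Analysis, for the behaviour checklist and sleep scale scores:

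1. Replace the change-score comparison with a between-arm comparison of scores at t1 and at t2 by ANCOVA, with the pre-lockdown score as covariate.
2. State the baseline date for each outcome, including which of the two measurements serves as t0 for screen time and physical activity.
3. State that within-arm change in these scores will not be interpreted as an effect of the programme.
4. If the two scales were in fact repeated before delivery, say so in the Results section and use that measurement as the covariate.

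Adding the scales to the pre-delivery contact would have been the better remedy, but on the article's own dates it is no longer available: delivery began in November 2020 and the article appeared in February 2021. The changes above cost only wording. They need no further visits or data, and ANCOVA spends one degree of freedom on the covariate slope, which is negligible with 440 participants enrolled.
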